## **Abstract**

### **Background**

Women with a history of gestational diabetes mellitus (GDM) are at high risk of progressing to type II diabetes mellitus (T2DM) and require frequent screening after delivery for early detection and intervention. In addition, their children may have an increased risk for overweight and obesity during their lifespan. Such data are not available in South Africa and the sub-Saharan African region, where the potential factors that may increase the risk of progression to T2DM as well as the metabolic syndrome may differ from risk factors in high income countries. These include high rates of food insecurity and obesity co-existing with undernutrition together with a potentially different genotype.

The overall objective of this study is to determine the prevalence of and risk factors for T2DM in postpartum women from low socioeconomic urban settings in South Africa who were diagnosed and treated for GDM 5 years ago in the public healthcare system.

## **Methods**

The proposed cross-sectional study will take place at a referral centers (the Groote Schuur Hospital) over a period of 12 months. Women treated for GDM 5 years previously, identified from the existing registers, who fit the inclusion criteria will be contacted and invited to participate.

Each participant will be expected to participate for around 2 hours. Participants will undertake a 2-hour oral glucose tolerance test as well as a 30 – 45-minute interviewer administered questionnaire. Additional data will be collected through a review of medical records for all participants.

## **Key Words**

Gestational diabetes, type II diabetes mellitus, glycated hemoglobin (HbA1c), metabolic syndrome, epidemiology, South Africa

## **Abbreviations**

DM – diabetes mellitus

GDM – gestational diabetes mellitus

T2DM – type II diabetes mellitus

HbA1c – glycated hemoglobin

OGTT – oral glucose tolerance test

IDF – international diabetes federation

## **1. Background**

Diabetes mellitus (DM) is one of the leading causes of morbidity and mortality in the world, with an estimated global prevalence of 9% in 2014 (1) and 1.5 million deaths directly related to DM in 2012 (2). At least 80% of DM related deaths occur in low- and middle-income countries (2). Around 90% of all DM cases are Type 2 diabetes mellitus (T2DM) (3). In South Africa, recent evidence shows that the prevalence of DM is increasing in urban dwelling South African populations (53% increase in prevalence during the period 1990 - 2012), including among women of child bearing age (4). The latest estimates are that the overall prevalence of diabetes in South Africa is 9% (5). The rising prevalence of non-communicable diseases like T2DM will add a considerable burden to an already struggling South African health system.

### **1.1.1 Gestational diabetes and prevalence of type 2 diabetes mellitus**

Gestational diabetes mellitus (GDM) is a known risk factor for the development of T2DM (6). Initially GDM was defined as glucose intolerance first presenting in pregnancy with return to normal glucose tolerance post pregnancy (6). More recent definitions include both women with pre-existing diabetes first recognized in pregnancy and women who manifest glucose abnormalities for the first time during pregnancy. There is still no consensus on the mechanisms underlying the development of GDM, although greater insulin resistance in GDM women compared to matched pregnant controls during the third trimester of pregnancy has been reported by several authors (7-9), lending weight to the role played by insulin resistance in the pathophysiology of GDM.

Several studies have demonstrated that the prevalence of GDM varies in different populations (10-12), because this is directly related to the specific population prevalence of T2DM. Recent systematic reviews of the small number of available studies in Africa estimate GDM prevalence to be between 0 and 14% (13). In South Africa, evidence from an ongoing unpublished study (Soweto pilot study) estimates the GDM prevalence to be higher than 15%.

Systematic reviews, primarily based on data from high income countries have reported that women with previous GDM have a seven-fold risk of developing T2DM (6,14), increased risk of long term cardiovascular disease (15,16) and risk of adverse perinatal outcomes for the GDM offspring (15,16). Research from high income countries has also shown that the majority (around 50%) of the women who progress to T2DM after GDM do so within the first 5 years after the GDM pregnancy (17). In addition, the prevalence of T2DM in women with

previous GDM varies widely in different populations, Kim et al, for example, found that T2DM prevalence ranged from a low 3% in some populations to as high as 70% in other populations (17). There is no data on the proportion of women with previous GDM who progress to T2DM and associated risk factors in Sub-Saharan Africa where, unlike the high-income countries, there are high rates of food insecurity and obesity co existing with malnutrition together with a potentially different genotype.

## **1.2 Rationale and Motivation**

Although evidence from systematic reviews suggests that GDM is a risk factor for T2DM, the extent of this risk is not known in Africa nor are the factors associated with the risk of development of T2DM. The T2DM disease burden in this high-risk population is not known in sub-Saharan Africa. The factors that may increase the risk of T2DM development in this vulnerable group may differ to those identified in high income countries. Any future interventions for the prevention of T2DM in women with a history of GDM need to be informed by evidence which is specific to the African context.

### **1.2 Aim and Objectives**

The aim of the study is to determine the prevalence of and risk factors for T2DM in women who had GDM 5 years previously, in South Africa.

The aim will be achieved by the following objectives;

#### **1.3.1 Objectives**

1. To estimate the prevalence of T2DM in women who were diagnosed and received management for GDM 5-6 years previously by using a glucose tolerance test to identify women with T2DM.
2. To investigate the other subsequent factors for the development of T2DM in women who were diagnosed and received management for GDM 5-6 years previously.

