## **Methods**

### **2.1 Research Design**

We will conduct a cross-sectional study to estimate the prevalence of T2DM and analyze possible risk factors in women with previous GDM.

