## **2.7 Questionnaire**

The questionnaire will have:

- Demographic data section– data on age, level of education, marital status, area of residence, employment status and ethnicity. Ethnicity will be self-reported and care will be taken to include an “other” option for ethnicity to accommodate participants who may not be comfortable in disclose their ethnicity.
- Medical history – data on comorbidities e.g. hypertension, post GDM pregnancy breastfeeding, family history of Type 2DM, parity, self-reported postnatal DM followup and current medications including anti-retroviral therapy.
- Other variables – data on smoking history, alcohol use history, psychosocial health, diet and physical activity will be assessed using established methods (4).

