## **2.8 Anthropometry and blood pressure**

Height, weight, and waist and hip circumferences will be measured using standardized techniques (34).

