### **2.13.2 Statistical data analysis**

All statistical analysis will be carried out using Stata 14 (37). For all analysis, the level of significance will be set at 0.05, 2-sided p-values and 95% Confidence Interval (95% CIs) will be reported. Crude T2DM prevalence will be calculated taking into consideration the sample design and the realized sample (4). For categorical variables frequencies and proportions will be reported, while bar graphs and pie chart will be used to present data where appropriate. The chi squared test, Fischer's Exact (small frequencies) and McNemar's chi squared Test (paired data) will be used to compare categories.

All continuous data will be tested for Normality using the Shapiro Wilks test and histogram plots. Means and standard deviations will be presented for variables that are normally distributed while medians and IQRs will be reported for variables that do not follow the Normal Distribution. Box and whisker plots, histograms, scatter plots and line graphs will be used to present data where appropriate. The t-tests and ANOVA (more than two groups) will be used to test to compare continuous outcomes between groups if data are normally distributed. For data that are not normally distributed, comparisons will be tested using Mann U Whitney, Wilcoxon sum rank (2 independent groups), Wilcoxon rank tests (paired data) as well as the Kruskal-Wallis for more than two groups.

Multivariate logistic regression, will be used to evaluate risk factors. Odds Ratios (ORs), their 95% CIs and p-values will be reported. Variables with p-values below 0.1 in the univariate analysis will be considered for the multivariate logistic regression. Additional analysis will include subgroup analysis for different ethnicities, should ethnicity prove to be an independent predictor of risk of T2DM.

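### Objective 2 asks about onset of T2DM, but index-pregnancy factors and factors measured at the 5-6 year visit share one screen and one logistic model in a cross-sectional study that can include women already treated

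*Protocol*

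**What the plan says.** The second objective (Protocol, 1.3.1) is "To investigate the other subsequent factors for the development of T2DM" in women managed for GDM 5-6 years earlier. The design statement (2.1) reads "We will conduct a cross-sectional study to estimate the prevalence of T2DM and analyze possible risk factors in women with previous GDM".

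Candidate factors come from two points in time:

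- **Index pregnancy.** The chart review (2.6) covers, among other items, age, the OGTT result at GDM diagnosis, insulin and oral agent use, booking BMI, birthweight and diabetes therapy at discharge.
- **The study visit.** The questionnaire (2.7) provides that "data on smoking history, alcohol use history, psychosocial health, diet and physical activity will be assessed using established methods". It also records self-reported postnatal diabetes follow-up and "current medications including anti-retroviral therapy". Section 2.8 adds "Height, weight, and waist and hip circumferences will be measured using standardized techniques", and section 2.9 adds a lipogram.

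Section 2.13.2 then states "Multivariate logistic regression, will be used to evaluate risk factors". Any variable with a univariate p-value below 0.1 is considered for that model. The rule does not refer to when a variable was measured.

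Only diabetes known before the index pregnancy excludes a woman from the study (2.3.2). Current T2DM treatment is listed as an exclusion for the HbA1c test only. Under 2.9, treated women need not do the OGTT or the HbA1c.

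**The concern.** A factor for the development of a disease has to precede it. Most index-pregnancy variables do so with respect to later T2DM. Visit-time variables need not: a woman diagnosed two years before the visit may since have changed her diet, activity or weight, and the questionnaire records the changed state. Her odds ratio contribution then describes what diagnosis did to the habit, not what the habit did to her risk.

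Two consequences follow from the rule as stated. First, modifiable factors can appear weaker than they are, null, or reversed. These are the natural targets of the preventive interventions that section 1.2 (Rationale and Motivation) wants the results to inform. Second, where booking BMI and current weight or waist enter together, the booking BMI coefficient loses whatever part of its effect passes through later weight. The second problem does not depend on anyone having been diagnosed.

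**Working it through.** **The plan's own figure.** The only computed design figure is the sample size in 2.11. With p = 0.40, z = 1.96 and d = 0.05, n0 = 0.40 × 0.60 × 1.96² / 0.05² = 368.8. With a finite population correction for 498 women, 368.8 / (1 + 367.8/498) = 212.1, rounded up to 213, which agrees with the stated number. It concerns prevalence and is not in dispute here. The illustration below uses the expected recruitment of 50% of 498 = 249 women, hence 0.40 × 249 = 99.6 cases and 149.4 non-cases.

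**Inputs that the documents do not give (assumed).**

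- Exposure: an unfavourable habit present in e = 50% of non-cases.
- k: share of cases diagnosed before the visit, 10% to 75%.
- c: share of exposed, diagnosed cases who dropped the habit afterwards, 10% to 50%.
- All diagnosed women count as cases.

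**Null factor (true OR = 1).** Before diagnosis 50% of cases are exposed. At the visit the exposed share among cases is e1 = 0.50 × (1 − kc). Because the odds among non-cases are 1, the observed OR is e1 / (1 − e1). For k = c = 50%: e1 = 0.50 × 0.75 = 0.375, and OR = 0.375 / 0.625 = 0.60.

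The chance of passing the p<0.1 screen in the false protective direction comes from the usual normal approximation for two proportions. For k = c = 50%, the difference is 0.125, the pooled standard error 0.0644 and the unpooled one 0.0635. So (0.125 − 1.645 × 0.0644) / 0.0635 = 0.30, a probability of 62%. With no bias it would be 5%.

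**Factor with true OR = 2.** The exposed share among cases is 2/3 before diagnosis and (2/3)(1 − kc) at the visit. For k = c = 25%: 0.6667 × 0.9375 = 0.625, and OR = 0.625 / 0.375 = 1.67.

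| k | c | Observed OR, true OR 1 | Passes screen as protective | Observed OR, true OR 2 |
|---|---|---|---|---|
| 10% | 10% | 0.98 | 6% | 1.94 |
| 10% | 50% | 0.90 | 10% | 1.73 |
| 25% | 25% | 0.88 | 12% | 1.67 |
| 25% | 50% | 0.78 | 25% | 1.40 |
| 50% | 25% | 0.78 | 25% | 1.40 |
| 50% | 50% | 0.60 | 62% | 1.00 |
| 75% | 50% | 0.45 | 91% | 0.71 |

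These figures cover one direction of change only. If diagnosed women took up the exposure instead, the bias would run upwards.

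**Who counts as a case.** Section 2.4 defines the main outcome by the OGTT, and section 2.9 spares treated women that test. The protocol does not say whether they enter the regression as cases. If they do, k can be substantial. If they do not, k falls to women diagnosed but not on treatment, and the figures move towards the top row. The loss of part of the booking BMI effect is the same either way.

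**The case against.** The best defence has three parts.

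*The protocol declares its design openly and does not speak of causes.* Section 2.1 calls the factors possible risk factors, and the rationale also speaks of association. A reader might infer that the plan claims causal effects; the text does not go that far. Objective 2 does, however, name development as the target, and the rationale links the results to prevention, so the wording still needs to match what the data can show.

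*Covariate lists, tiers and sensitivity models belong in a statistical analysis plan, which is not shown.* This is fair as far as it goes. A reader might infer that diabetes drugs and postnatal follow-up will be entered as predictors, but no covariate list says so, and screened variables are only considered for the model. What remains is fixed in the protocol itself: the objective's wording and a single screen and model without regard to timing.

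*The size of the bias is unknown.* This stands. A reader might infer that many participants had been diagnosed and counselled. The documents give no share, and the only lifestyle advice they describe comes at the end of the study (2.14), after exposures are measured. It is also easy to choose one pair of assumptions at which an association vanishes, such as 50% and 50% above; that is one point in a range that starts near no bias at all.

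Nor should index-pregnancy factors simply be made the primary analysis. Objective 2 asks about subsequent factors, so doing that would demote its own subject. Index-pregnancy data are not guaranteed to precede onset either: section 1.1.1 notes that newer GDM definitions take in diabetes first recognised in pregnancy, and section 2.3.2 excludes only known prior diabetes.

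**Conclusion.** The point holds in a limited form. The stated rule mixes factors recorded in the index pregnancy with factors measured alongside the outcome, under an objective about onset, in a study that women already treated for T2DM can join. Followed as written, it can give attenuated or reversed odds ratios for visit-time factors and can understate booking BMI.

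Under the assumed shares, a null factor would show an OR from about 0.98 to 0.45, and a true OR of 2 would show as anything from 1.94 to 0.71. The documents do not say where in that range the study will fall. The result depends on the share of cases already diagnosed, on how many changed habits, and on whether treated women count as cases. The booking BMI argument needs none of these; it needs only that current weight or waist enters the same model. The prevalence objective and its sample size are unaffected.

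**What to change.** In section 2.13.2:

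1. Fit one model of index-pregnancy and fixed factors: the 2.6 chart data except diabetes therapy at discharge (which may reflect persisting diabetes), plus age, family history and ethnicity. Do not adjust it for visit-time variables.
2. Fit visit-time factors in a separate model, reported as cross-sectional associations. Leave out glucose-lowering medication and postnatal diabetes follow-up as predictors.
3. Repeat the second model as a sensitivity analysis without women whose T2DM was known before the visit.

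In section 1.3.1, reword Objective 2 so that visit-time exposures are described as associated with T2DM.

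The cost is wording and one extra model, using data already planned for collection. The sensitivity analysis will have fewer cases, and they will be a selected group (newly detected T2DM only), so it should be read as a check beside the second model and not as its replacement.

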## **Methods**

### **2.1 Research Design**

We will conduct a cross-sectional study to estimate the prevalence of T2DM and analyze possible risk factors in women with previous GDM.

### **2.2 Study Setting**

The study will take place at a tertiary referral center, in the Western Cape Province (Groote Schuur Hospital).

### **2.3 Study population and sampling procedures**

In the major South African cities, all women with GDM are managed at tertiary hospitals. Eligible participants who were managed for GDM during 2010 to 2011 at Groote Schuur

academic hospital will be identified from hospital registers and invited to participate in the study. The study involves women who had gestational diabetes 5 years ago and currently we have been calling them and asking them to come to Groote Schuur hospital for participation, in Cape Town. However, most of the contact numbers are now obsolete and we would like to amend the protocol to include that:

- a. Home visits will be made where applicable, to recruit participants
- b. Instead of the oral glucose tolerance test, a fasting blood glucose, fasting lipids as well as HbA1C will be made at community centers near the participants' locations in the case of participants who are unable to come to the Groote Schuur.

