## **2.4 Measurements**

Diabetes as defined by the result of the 75g 2hour OGTT, as defined according to the WHO 2006 guidelines will be the main outcome. Other outcomes will include impaired fasting glucose and impaired glucose tolerance.

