## **2.9 Oral Glucose Tolerance Test and HbA1c**

Participants will be given 75g anhydrous glucose in 250ml of water, in the morning after a 10-12 hour overnight fasting period (3). Venous blood samples will be taken at 0 minutes for glucose, lipogram and for HbA1c measurement, at 30 minutes and 120 minutes for glucose

and insulin. The bloods will be kept on ice, and sent to the laboratory for handling and measurement of the same day using commercially available test kits. T2DM will be diagnosed according to WHO guidelines (3). One additional blood sample (5ml each) will be taken from each participant, centrifuged and the serum stored in case some samples get spoiled or if confirmation is needed or an additional investigation relating to GDM is considered. The samples will be stored up to 5 years after the study and thereafter destroyed. Ethics approval will be sought if any additional investigations are performed. Any participants who are already on treatment for T2DM will not be required to do either the OGTT or the HbA1c.

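### The community route drops the OGTT, but the main outcome and IGT still depend on it, so women who cannot come to the hospital have no defined outcome

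*Protocol*

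**What the plan says.** All references are to the Protocol.

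- Section 1.3.1 (objective 1) estimates prevalence "by using a glucose tolerance test to identify women with T2DM".
- Section 2.4 fixes the endpoint: "Diabetes as defined by the result of the 75g 2hour OGTT, as defined according to the WHO 2006 guidelines will be the main outcome". It adds: "Other outcomes will include impaired fasting glucose and impaired glucose tolerance".
- Section 2.3(b) states: "Instead of the oral glucose tolerance test, a fasting blood glucose, fasting lipids as well as HbA1C will be made at community centers". This applies "in the case of participants who are unable to come to the Groote Schuur". The reason given for amending recruitment is that "most of the contact numbers are now obsolete".
- Section 2.9 describes the hospital visit: "Venous blood samples will be taken at 0 minutes for glucose, lipogram and for HbA1c measurement", with glucose and insulin again at 30 and 120 minutes. It refers diagnosis to WHO guidelines, citing the 1999 report, whereas section 2.4 names the 2006 guidelines. Participants already treated for diabetes skip both the OGTT and the HbA1c.
- Section 2.3.2 removes women treated for chronic renal failure, iron deficiency anaemia or T2DM from the HbA1c analysis.
- Section 2.13.2 plans crude prevalence and logistic regression for risk factors, and names no term for testing route.

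**The concern.** Section 2.3(b) enrols women who will have no 2-hour glucose, and the sections that define and analyse the outcome were not changed to match. Such a woman cannot meet a 2-hour criterion and cannot be classified for IGT. The protocol gives no fasting-only or HbA1c case rule for her. If she is pooled with women who had an OGTT, two case definitions are mixed. If she is dropped, the study loses the women whom the change was meant to recover. The route follows inability to attend, so it is not a random split. Both the prevalence estimate and the risk-factor odds ratios are exposed.

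**Working it through.** **The plan's own figure.** Section 2.11 gives p = 0.40, d = 0.05, z = 1.96 and a population of N = 498.

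- n0 = p(1-p)z²/d² = 0.40 × 0.60 × 1.96² / 0.05² = 368.8.
- With the finite population correction, N·n0/(n0 + N - 1) = 498 × 368.8 / 865.8 = 212.1, rounded up to 213. The stated 213 is reproduced.
- At the expected 50% recruitment (249 women), the half-width is 1.96 × √[(0.24/249) × (249/497)] = 0.043, or 4.3 points.

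**Inputs that the protocol does not give (assumed).** f is the share tested by the community route. s is the sensitivity of the substitute rule against the OGTT definition, among untreated cases. Sp is its specificity. u is the share of cases not already treated. Treated women are taken to count as cases on both routes, and true prevalence is taken as 40% on both.

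**Bias in overall prevalence** = -f·p·u·(1-s) + f·(1-p)·(1-Sp).

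With u = 1 and Sp = 1, in percentage points:

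| s | f = 0.1 | f = 0.3 | f = 0.5 |
|---|---|---|---|
| 0.9 | -0.4 | -1.2 | -2.0 |
| 0.7 | -1.2 | -3.6 | -6.0 |
| 0.5 | -2.0 | -6.0 | -10.0 |

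The bias reaches 5 points when s = 1 - 0.05/(f × 0.40), that is, 0.58 at f = 0.3 and 0.75 at f = 0.5.

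**Treated women.** They skip the OGTT on either route (section 2.9), so the change of test cannot cause them to be missed. The table is therefore an upper range. With u = 0.5 every cell halves:

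- f = 0.3, s = 0.7: 0.3 × 0.40 × 0.5 × 0.3 = 1.8 points
- f = 0.5, s = 0.7: 3.0 points
- f = 0.5, s = 0.6: 4.0 points

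**Direction.** A fasting-only rule drops one criterion from the OGTT definition, so it can only miss cases (Sp = 1). This assumes that the WHO definition accepts either a fasting or a 2-hour value, since the protocol prints no cut-offs. If HbA1c is also diagnostic, false positives offset the loss. At f = 0.5, s = 0.7 and u = 1:

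- Sp = 0.9: -6.0 + 0.5 × 0.60 × 0.1 × 100 = -3.0 points
- Sp = 0.8: -6.0 + 6.0 = 0

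**Risk factors.** Take a covariate with no true effect, present in 60% of community and 40% of hospital women, with u = 1 and Sp = 1. At f = 0.5 and s = 0.5, apparent prevalence is 0.6 × 0.20 + 0.4 × 0.40 = 0.28 with the factor and 0.4 × 0.20 + 0.6 × 0.40 = 0.32 without it. The spurious OR is (0.28/0.72)/(0.32/0.68) = 0.83. At f = 0.3 and s = 0.8 the prevalences are 0.369 and 0.382, and the OR is 0.94.

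**IGT.** If community women stay in the denominator but cannot enter the numerator, apparent IGT prevalence is (1-f) times the true value, given equal true prevalence on both routes. At f = 0.3 it is understated by 30% in relative terms.

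**The case against.** The community route is reasonable in itself. Without it, women who cannot travel are lost and selection bias replaces ascertainment bias. This stands: the fault lies in the unmatched outcome definition, not in testing near home.

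The reference to WHO guidelines in section 2.9 might be said to supply a fasting rule. It does not settle the matter. It cites a different edition from section 2.4, no HbA1c case rule appears anywhere, and section 2.4 ties the main outcome to the OGTT.

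An unseen SAP may deal with pooling, imputation and adjustment. That is fair for the analysis, and the protocol commits to neither pooling nor dropping. The definition of the main outcome, however, is protocol content, and there it conflicts with section 2.3(b).

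Some stronger readings are tempting, but the protocol does not support them:

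- A reader might infer that prevalence will be biased down by about 4 to 8 points. That rests on selected values of f and s, on every case being untreated, and on perfect specificity.
- A reader might infer that any covariate linked to inability to travel acquires a protective odds ratio near 0.58. That figure is the OR for route itself at s = 0.7, (0.28/0.72)/(0.40/0.60), or 0.77 if half of the cases are treated. Route is not a planned risk factor, and a covariate only correlated with it is distorted much less.
- Obsolete telephone numbers do not show that the community share is large. They explain why home visits are needed, not how many women cannot attend.
- The protocol does not say that route depends on distance, employment or ethnicity. It says only that these women are unable to come.

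**Conclusion.** Wrong as written. The contradiction between section 2.3(b) and sections 1.3.1 and 2.4 is explicit, and it leaves the main outcome undefined, or differently ascertained, in a group that the study deliberately enrols. IGT cannot be determined in that group.

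The resulting bias is of unknown size. Its direction is downward under a fasting-only rule and uncertain if HbA1c counts. It concerns only women not already treated for diabetes. Under the stated assumptions it could be negligible (-0.4 points) or exceed the 5-point target (-10 points at the extreme, -5 if half of the cases are treated). Spurious odds ratios for a null covariate correlated with route are modest, about 0.83 to 0.94 in the example. Confidence is high for the contradiction and low for any single bias figure.

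**What to change.** Amend sections 2.4 and 2.13.2, and align 1.3.1 and 2.9 with them, naming one WHO edition throughout.

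1. Report prevalence and fit the risk-factor model for all women on one definition available on both routes: treated T2DM diagnosed since the index pregnancy, or the fasting criterion of the WHO definition named. Add HbA1c only in a version that respects the section 2.3.2 exclusions.
2. Report OGTT-defined prevalence in hospital-tested women, counting treated women as cases. As a sensitivity analysis, extend it to all women by multiple imputation of the 2-hour result in untreated community women. Train the model on untreated hospital women, because treated ones have no OGTT. State the missing-at-random assumption, which matters because route is not random.
3. Restrict IGT to women with an OGTT, in both numerator and denominator.
4. Enter testing route as a covariate in a sensitivity analysis only. Under a common definition the difference in tests is gone, and route in the main model could over-adjust for factors such as residence or employment.

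The cost is wording and modest extra analysis. Both routes already collect fasting glucose and HbA1c, so no new samples are needed, and the required sample size stays at 213. The drawbacks are more than one prevalence figure, a wider interval for the imputed one, and a common definition that misses cases visible only at 2 hours.
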